### Study groups

2.6

Participants are randomly assigned to one of six groups (arms) in a 1:1:1:1:1:1 ratio. Four groups are primary comparison arms for the main efficacy analysis at 6 weeks, and two additional groups are included for secondary analyses of conditioned stimulus specificity in Phase 2.

**Group 1: Hypnosis** + **Essential Oil (Bergamot).** Participants receive the self-hypnosis audio and inhale bergamot essential oil during each session in Phase 1. In Phase 2, they continue with bergamot oil only (no audio) on the same schedule. This is a conditioned stimulus (CS)-match condition where the same essential oil is used for conditioning and testing.

**Group 2: Hypnosis** + **Essential Oil (Lavender).** Participants receive the hypnosis audio plus lavender essential oil inhalation during Phase 1 sessions. In Phase 2, they use lavender oil only without hypnosis. This is the CS-match for lavender.

**Group 3: Hypnosis Only (No Oil).** Participants receive guided hypnosis sessions in Phase 1 with no aromatherapy. This controls for the effects of hypnosis alone. They do not use any aroma in Phase 2 either and effectively have no active intervention in weeks 7–8.

**Group 4: Minimal Intervention Control.** Participants do neither hypnosis nor essential oil in Phase 1. Instead, they may receive a minimal activity just to match time/expectation. This arm serves as a baseline and expectancy control. They also do not receive any aroma in Phase 2.

**Group 5: Hypnosis** + **Oil (Bergamot) → Switch to Lavender.** These participants start identical to Group 1 (hypnosis + bergamot oil in Phase 1). However, in Phase 2 they experience a CS-mismatch by switching to lavender without hypnosis. This group helps test if a different scent can trigger relaxation or if the effect is lost when the conditioned stimulus changes. It serves as a control for Group 1 in the conditioning analysis.

**Group 6: Hypnosis** + **Oil (Lavender) → Switch to Bergamot.** These participants mirror Group 2 initially (hypnosis + lavender in Phase 1), then switch to bergamot oil only in Phase 2, creating a CS-mismatch. This serves as a control for Group 2 to assess stimulus specificity.

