All groups 1, 2, 5, and 6 receive the full combined intervention (hypnosis + essential oil) in Phase 1, ensuring that Groups 5 and 6 have the same conditioning opportunity as their counterparts before the switch. Groups 3 and 4 allow us to isolate the effects of hypnosis itself (Group 3) and to account for any changes over time not attributable to the interventions (Group 4). Randomization is implemented via the SoSci Survey platform's built-in algorithm once participants are deemed eligible, ensuring allocation concealment. Because of the nature of the interventions, participants will know if they are using an oil or not (blinding is not feasible on the user level), but they will not be informed of the study hypotheses regarding which combination is expected to be most effective. The trial is single blinded in that the data analysts/statisticians will remain blind to group labels until after the primary analyses are completed, to prevent bias in outcome analysis.

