### Physiological subgroup

2.8

To complement self-reported outcomes with physiological data, the study includes an optional physiology component for a subset of participants. Up to 15 participants per group (approx. n≈90 total) who live in the Berlin/Brandenburg region will be invited to attend laboratory sessions at the Charité – Virchow Clinic Campus in Berlin. Electrophysiological measurements will be performed over a 15-min period during which the participant is at rest and in a supine position in the electrophysiological laboratory. During this period, the ECG and pulse are recorded using wearables. Electrophysiological measurements are to be recorded at two time points: initially at the baseline (T0) and subsequently following the six-week intervention period (T1). The ECG and pulse raw data indices were utilized to derive HRV and pulse wave variability (PWV), which are indices of autonomic nervous system (ANS) activity. The activity of the sympathetic nervous system (SNS), the parasympathetic nervous system (PNS), or both components of the ANS is indicated by these indices. In the course of each and every recording session, the participants were equipped with a Polar H10 chest-strap heart rate sensor (for the purpose of recording ECG for HRV) and a Polar Verity Sense optical pulse sensor (for the purpose of PWV via photoplethysmography). It is hypothesized that the response to the various 6-week interventions would be subject to change, and that the before-and-after effect would vary in the autonomous variables depending on the nature of the intervention. This methodology facilitates the representation of variation in dynamic changes across groups and over time. A comparison of the time points T0 and T1 will facilitate objective and quantitative mapping of the dynamic changes caused by the interventions. The autonomous measurements will facilitate the characterization of the interventions in terms of their mechanisms of action, and the extent to which each intervention leads to the assumed subjective improvement in relaxation/recovery (increased PNS). In addition, the study will elucidate the way this intervention enhances autonomic-vegetative function in the short term. The utilization of HRV and PWV in the time domain, in the frequency domain and nonlinear dynamics, has been demonstrated to be a reliable indicator of changes in sympathovagal balance (19). A greater HRV (particularly high-frequency HRV) and a slower PWV (which reflects vasodilation and reduced arterial stiffness) would suggest a shift towards parasympathetic dominance and relaxation. It is hypothesized that the combination of hypnosis and essential oils may result in increased relaxation, which is further enhanced by the intervention and over time from T0 to T1 in comparison to the hypnosis-only group. This is consistent with the hypothesis that deeper or more effective relaxation training is achieved through this method. The resultant phenomenon is evidenced by a decline in sympathetic tone and an augmentation in vagal tone, culminating in a state of profound relaxation and recuperation through the deactivation of the ANS.

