**Exploratory Hypothesis 2.3 (Moderators of Effect).** We will explore whether certain baseline factors moderate the intervention's effectiveness. Demographic factors like age, gender, or socioeconomic status might influence outcomes. For instance, it's possible that participants with higher initial anxiety, though still subthreshold, benefit more or less from the intervention, or that younger vs. older participants have different adherence rates. These analyses are exploratory and will be used to generate hypotheses for which subgroups respond best to this approach.

**Exploratory Hypothesis 2.4 (Physiological Effects).** We hypothesize that the combination of hypnosis and aromatherapy yields measurable physiological relaxation, reflected in increased parasympathetic activity or reduced sympathetic activity compared to hypnosis alone. In the laboratory subgroup, it is hypothesized that Group 1/2 (combined) will demonstrate larger increases in HRV, particularly high-frequency HRV, which is indicative of parasympathetic tone, and/or a greater reduction in heart rate and PWV from T0 to T1 than Group 3 (hypnosis only). This would suggest an additive effect of the essential oil on the body's relaxation response, consistent with objective evidence that an essential oil can modulate autonomic activity. However, given sample size limitations, this will be an exploratory outcome.

**Exploratory Hypothesis 2.5 (VAS Trajectory and Learning Effects).** By examining the VAS relaxation ratings collected before and after each session, we hypothesize that participants receiving the combined intervention will not only have larger acute relaxation gains per session on average than those in comparison groups, but they may also exhibit learning effects over time. A learning effect would manifest as gradually higher pre-session relaxation levels as weeks progress the participant's baseline state before each session improves, indicating they carry over some relaxed state or become more skilled at self-relaxation. We expect such effects might be most pronounced in those who undergo conditioning (Groups 1 and 2), potentially showing an upward drift in pre-session VAS scores and/or a plateau indicating habituation to relaxation. We will explore and graph these trajectories for insight into how the relaxation response develops with practice.

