### Biosignal processing

2.12

A total of 15 min of ECG (130 Hz) and photoplethysmographic (PPG; 28 Hz) data will be collected from all participants of the sub-study during the resting conditions at T0 and T1. The ECG data will be recorded using a Polar H10 chest-strap, and the PPG data will be recorded using a Polar Verity Sense optical pulse sensor. The participants will remain in a seated position during the recording. The time series estimating functions of the autonomic regulation will be semi-automatically extracted from the raw data using Kubios HRV Scientific Software for the ECG and an in-house software (programming environment Matlab R2025a) for the PPG, derived as follows:
time series of heart rate, consisting of successive beat-to-beat intervals [BBI, (ms)],time series containing maximum PPG peak amplitudes per heartbeat [PPGMAX, (a.u.)], andtime series containing minimum PPG peak amplitudes per heartbeat [PPGMIN, (a.u.)].Afterwards each 15-min time series will be filtered by applying an adaptive variance estimation algorithm to remove and interpolate ectopic beats and artefacts to ensure normal-to-normal time series (NN) (21). Afterwards indices describing autonomic regulation will be calculated in the time domain (TD), in the geometric domain [Baevsky's stress index (22)], the frequency domain (FD) (the power spectra of equidistant linear interpolated NN interval time series will be obtained by applying the Fast Fourier Transformation), and in the nonlinear domain (NLD) (Table 1).

**Table 1 T1:** Definition of clinically relevant HRV indices and their assignment to the autonomic nervous system.

Domain	Index	Unit	Definition and explanation	Activity as part of the autonomic nervous system
Time domain	meanNN	ms	Mean value of all NN intervals	—
	SDNN	ms	Standard deviation of NN intervals in the measurement time range	Sympathetic nervous system and parasympathetic nervous system
	SDANN	ms	Standard deviation of the average of NN intervals in 5-min segments	Sympathetic nervous system and parasympathetic nervous system
	RMSSD	ms	“Root Mean Square of successive differences” (Square root of the mean value of the sum of all squared differences between adjacent NN intervals)	Parasympathetic nervous system
	NN50	beats	Number of pairs of adjacent NN intervals that differ by more than 50 ms	Parasympathetic nervous system
	pNN50	%	Percentage of consecutive NN intervals that differ by more than 50 ms	Parasympathetic nervous system

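### Equal caps across six arms give hypnosis-only, the sole comparator in H2.4, 15 of the 90 physiology slots, although only Phase 1 treatment differs when recordings end

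*Protocol article*

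**What the plan says.** Section 2.8 (Physiological subgroup) offers laboratory sessions to "Up to 15 participants per group (approx. n≈90 total) who live in the Berlin/Brandenburg region". On timing it states: "Electrophysiological measurements are to be recorded at two time points: initially at the baseline (T0) and subsequently following the six-week intervention period (T1"). Section 2.12 (Biosignal processing) agrees: the data are collected "during the resting conditions at T0 and T1".

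Section 2.6 (Study groups) has participants "randomly assigned to one of six groups (arms) in a 1:1:1:1:1:1 ratio". It says of Phase 1: "All groups 1, 2, 5, and 6 receive the full combined intervention (hypnosis + essential oil) in Phase 1". Group 5 is described as follows: "These participants start identical to Group 1 (hypnosis + bergamot oil in Phase 1"). Group 6 mirrors Group 2 in the same way. The oils are switched only in weeks 7–8, after T1.

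Exploratory Hypothesis 2.4 (section 2.10) expects Groups 1 and 2 combined to show larger autonomic changes "from T0 to T1 than Group 3 (hypnosis only"). Section 2.8 also names hypnosis-only as the comparator, but there it describes the other side simply as hypnosis with essential oils, without group numbers. Both sections call the physiological analysis exploratory because the subgroup is small, and no power is claimed for it.

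**The concern.** Groups 5 and 6 exist to separate matched from mismatched scent in Phase 2. The sub-study never observes Phase 2, so that distinction cannot appear in any ECG or pulse recording. Equal caps nevertheless carry the six-arm structure into the laboratory, and the article gives no reason for doing so.

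At the last recording the 90 slots amount to 60 on hypnosis plus oil (30 bergamot, 30 lavender), 15 on hypnosis-only and 15 on minimal intervention. Two thirds of the laboratory effort falls on one side of the only physiological contrast the protocol names, and one sixth on the other. What is at stake is the precision of H2.4 for a fixed number of visits. The primary analysis is unaffected.

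**Working it through.** **Inputs.** Cap of 15 per arm, six arms, recordings at T0 and T1 (sections 2.6, 2.8, 2.12). Contrast of Groups 1 and 2 with Group 3 (section 2.10). Two-sided 5% level, d of about 0.35–0.40 and dropout of up to 35%, all from section 2.11. Those three were set for the main trial and the MDBF, so applying them to HRV is an assumption. A d of 0.8 is added purely for illustration.

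**The plan's own figure.** 15 × 6 = 90, as stated. Hypnosis plus oil: 4 × 15 = 60, or 67%. Hypnosis-only: 15, or 17%.

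**Formulas.** Variance factor V = 1/n₁ + 1/n₂. Standard error = SD × √V. The detectable d is the effect with 80% power under the noncentral t distribution; as an approximation it is 2.80 × √V. All effects are in SD units of the analysed change, at full attendance.

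| Combination vs hypnosis-only | V | SE (in SD) | Detectable d | Power at d 0.35 / 0.40 | Power at d 0.8 |
|---|---|---|---|---|---|
| 30 vs 15 (H2.4 as worded) | 1/30 + 1/15 = 0.100 | 0.316 | 0.91 | 19% / 23% | 70% |
| 60 vs 15 (current caps, all oil arms pooled) | 1/60 + 1/15 = 0.083 | 0.289 | 0.82 | 22% / 28% | 78% |
| 30 vs 30 (equal thirds by treatment) | 1/30 + 1/30 = 0.067 | 0.258 | 0.74 | 27% / 33% | 86% |
| 45 vs 30 (proposed caps) | 1/45 + 1/30 = 0.056 | 0.236 | 0.67 | 31% / 39% | 92% |

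**Where the limit lies.** Doubling the oil side from 30 to 60 lowers the standard error by only 9% (0.316 to 0.289), because the 15 in Group 3 dominate V.

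**Gain from reallotment alone.** The fair baseline is 60 vs 15, which the current caps already make available by pooling. Against it, 45 vs 30 cuts the variance by 33% (0.056/0.083 = 0.67) and the standard error by 18%. Equal thirds would cut them by only 20% and 11%.

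**With 35% dropout assumed.** 30 vs 15 becomes about 20 vs 10 (detectable d 1.12), 60 vs 15 about 39 vs 10 (1.01), and 45 vs 30 about 29 vs 20 (0.83).

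**If Group 3 does not fill.** With no slots reverting, 45 vs 15 gives 1/45 + 1/15 = 0.089, slightly worse than 0.083. The break-even is 17 recordings in Group 3: 1/45 + 1/17 = 0.081, while 16 gives 0.085. If the 15 unfilled slots revert to Groups 5 and 6, the contrast returns to 60 vs 15.

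**The case against.** The strongest case against is that nothing here is false or contradictory. The article calls the analysis exploratory, claims no power for it, and sets 15 as a ceiling. Equal caps follow naturally from 1:1 randomisation and tend to fill in parallel. All of that stands, and it is why this is only an inefficiency.

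Three further points also stand and shape the remedy:

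- **Other aims.** Section 2.8 wants to characterise each intervention, and the Introduction mentions comparing the two oils. Current caps give 30 recordings per oil at T1. The proposed caps give 22 to 23, so the bergamot–lavender variance factor rises from 1/30 + 1/30 = 0.067 to 1/22 + 1/23 = 0.089. Closing Groups 5 and 6 altogether would leave 15 per oil and double it to 0.133.
- **Recruitment.** Thirty slots in Group 3 need 30/105 = 29% of that arm as regional volunteers, against 14% now. Group 3 could also go on filling after the other arms are full, which would partly tie treatment to calendar time.
- **Conclusions.** At d 0.35–0.40 the sub-study remains underpowered under any split. Even 45 vs 45, with no minimal-intervention slots, gives only 38–47%.

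A reader might infer that Groups 5 and 6 are wasted and that 0.100 is therefore the right baseline. The documents do not support that. H2.4 does not name those arms, but section 2.8 words the combination without group numbers, and nothing rules out pooling. A reader might also infer that better caps would make H2.4 a properly powered test. They would not.

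**Conclusion.** The point holds as a modest, optional improvement. The caps follow a Phase 2 distinction that the recordings never reach, and this leaves the sole H2.4 comparator with 15 of 90 slots. Moving 15 slots from Groups 5 and 6 to Group 3, and pooling the oil arms, cuts the variance of the contrast by 33% relative to 60 vs 15 and brings the detectable d from 0.82 to 0.67.

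These figures assume that the slots fill, that everyone attends both sessions, that the SD is the same in all arms, and that the two oils may be treated as one combination, as H2.4 itself does. Counted by oil there are four Phase 1 regimens (30/30/15/15), and hypnosis-only still has 15. The analysis stays exploratory, and neither the validity of the trial nor its primary result depends on this.

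**What to change.** In section 2.8, keep the total at about 90 and replace the uniform cap with: Groups 1, 2 and 4, up to 15 each; Group 3, up to 30; Groups 5 and 6, 7 and 8 (15 together). The sum is 15 + 15 + 30 + 15 + 15 = 90. State that unfilled Group 3 slots revert to Groups 5 and 6. In H2.4, define the combination as Groups 1, 2, 5 and 6 pooled.

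The number of recordings does not change. The costs are the looser comparison between oils and the larger share of regional volunteers needed from Group 3. The combination vs minimal-intervention comparison also becomes slightly less precise (0.083 to 1/45 + 1/15 = 0.089), while hypnosis-only vs minimal intervention improves (from 1/15 + 1/15 = 0.133 to 1/30 + 1/15 = 0.100). To limit calendar-time imbalance, invite regional volunteers in each arm at rates proportional to the caps, so that the arms fill together. If the sponsor prefers to keep equal caps, pooling the four oil arms in H2.4 costs nothing and takes the variance factor from 0.100 to 0.083.

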Combining guided self-hypnosis with essential oil inhalation may yield synergistic benefits for relaxation. Hypnosis can induce a deep relaxation response, and pairing this state with a specific olfactory stimulus (the essential oil's aroma) opens the door for classical conditioning of relaxation. Through repeated pairings, the neutral scent of an essential oil could become a conditioned stimulus (CS) that evokes calmness even in the absence of hypnosis. In fact, prior work has explored hypnotherapeutic olfactory conditioning, where patients undergoing hypnosis learn to associate a pleasant odor with feelings of safety and control (10). Preliminary results using this technique in cases of post-traumatic stress showed promise that the scent alone later helped induce relaxation and reduce anxiety (10). This concept aligns with fundamental Pavlovian conditioning principles and suggests that a well-timed combination of aromatherapy and hypnosis could train individuals to self-soothe by simply inhaling the scent after conditioning.

The present study builds upon a successful trial in healthy individuals (11) and aims to rigorously test a multimodal relaxation intervention in subsyndromal anxiety. The predecessor study was a four-arm randomized trial with over 500 participants, which found that combining web-based self-hypnosis with an essential oil significantly increased subjective relaxation compared to either technique alone. Participants who received the combined hypnosis plus essential oil reported notably greater improvements on relaxation scales with moderate effect sizes relative to controls. Encouraged by these findings, this study will extend this approach to individuals with mild generalized anxiety symptoms and examine not only the acute efficacy but also the conditioning effect of the essential oil over time. In summary, the study's primary goal is to evaluate whether digital self-hypnosis combined with inhalation of an essential oil, either lavender or bergamot, can produce greater relaxation and anxiety reduction than hypnosis alone or minimal intervention, and secondarily to determine if the essential oil's scent can become a stand-alone cue for relaxation after repeated pairing with hypnosis as well as whether objective physiological measures such as heart rate variability (HRV) can prove a relaxation effect on the autonomic nervous system.

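### Section 2.8 attributes the T0-T1 change in HRV and PWV to the interventions, but the only named physiology contrast isolates the oil increment, and Group 4, though recorded, is not named as the reference for hypnosis or the whole package

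*Protocol article*

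**What the plan says.** All statements are in the protocol article.

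- **Who is measured, and when (Section 2.8).** "Up to 15 participants per group (approx. n≈90 total" are to be recorded at two time points, "initially at the baseline (T0) and subsequently following the six-week intervention period (T1". All six arms are therefore included, Group 4 among them.
- **What the change is taken to mean (Section 2.8).** "A comparison of the time points T0 and T1 will facilitate objective and quantitative mapping of the dynamic changes caused by the interventions". The autonomic measures are also to show "the extent to which each intervention leads to the assumed subjective improvement in relaxation/recovery (increased PNS".
- **Which comparator is named.** Section 2.8 expects more relaxation with hypnosis plus oil "over time from T0 to T1 in comparison to the hypnosis-only group". H2.4 in Section 2.10 expects larger changes in Groups 1/2 "from T0 to T1 than Group 3 (hypnosis only". No physiology contrast names Group 4.
- **General wording on groups (Section 2.8).** "This methodology facilitates the representation of variation in dynamic changes across groups and over time", without saying which groups are compared.
- **Aim (Introduction).** The study is to determine "whether objective physiological measures such as heart rate variability (HRV) can prove a relaxation effect on the autonomic nervous system".
- **Role of Group 4 (Section 2.6).** It is there to capture change over time that the interventions did not produce.
- **Status.** Sections 2.8 and 2.10 call the physiology exploratory. Section 2.13 describes no physiology model.

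**The concern.** The causal claim is wider than the comparison that would support it. Section 2.8 speaks of changes caused by the interventions and of what each one achieves, and the Introduction asks whether HRV can demonstrate relaxation. These are questions about the effect of hypnosis and of the full package. The named contrast compares two conditions that both contain hypnosis, so it answers only whether the oil adds something.

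Without a named control, the wider claims would rest on change from T0 to T1 within arms. Part of that change may be common to every arm. A supine or seated rest recording in an unfamiliar laboratory may look different at the second visit simply because the setting is now known.

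Two misreadings become possible. Drift shared by all arms could be reported as an autonomic effect of the intervention. Conversely, if hypnosis works and the oil adds nothing, the one named contrast is expected to be null, and the hypnosis effect is never compared with the control arm already recorded.

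**Working it through.** **1. Is Group 4 measured?** Section 2.8 gives up to 15 per group, with six groups: 15 × 6 = 90. This reproduces the stated total, so the substudy includes up to 15 Group 4 participants.

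**2. What each comparison estimates.** Let *s* be change shared by all arms between visits, *h* the effect of hypnosis relative to the minimal intervention, and *o* what the oil adds. The expected T0-T1 change is:

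| Arm | Expected change |
|---|---|
| Group 4 | *s* |
| Group 3 | *s* + *h* |
| Groups 1/2 | *s* + *h* + *o* |

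Hence:

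- Groups 1/2 minus Group 3 (the named contrast) = *o*; *s* cancels.
- Group 3 minus Group 4 (not named) = *h*.
- Groups 1/2 minus Group 4 (not named) = *h* + *o*.
- Within-arm change in Group 3 = *s* + *h*; in Groups 1/2 = *s* + *h* + *o*. Neither separates *s* from the treatment effect.

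**3. Illustration of what *s* could do.** The article gives no value for *s*, so 0.2 to 0.5 SD of the change score is an assumption. Set *h* = *o* = 0. For a one-sample t-test on change, two-sided 5%, the noncentrality is drift × √n with n − 1 degrees of freedom.

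| Assumed drift (SD) | n = 15: noncentrality | Probability of p < 0.05 | n = 30: noncentrality | Probability of p < 0.05 |
|---|---|---|---|---|
| 0.2 | 0.2 × √15 = 0.77 | 0.11 | 0.2 × √30 = 1.10 | 0.19 |
| 0.3 | 0.3 × √15 = 1.16 | 0.19 | 0.3 × √30 = 1.64 | 0.36 |
| 0.5 | 0.5 × √15 = 1.94 | 0.44 | 0.5 × √30 = 2.74 | 0.75 |

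Here n = 15 is one arm and n = 30 is Groups 1 and 2 pooled. For any between-arm contrast of change, including the named one, *s* drops out and the rate is the nominal 5%.

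**4. What contrasts with Group 4 can detect.** For a two-sample t-test on change, the noncentrality is d / √(1/n₁ + 1/n₂). Solving for 80% power at two-sided 5%:

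- 15 v 15 (Group 3 v Group 4): √(1/15 + 1/15) = 0.365, giving d ≈ 1.06 SD.
- 30 v 15 (Groups 1/2 v Group 4): √(1/30 + 1/15) = 0.316, giving d ≈ 0.91 SD.

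These assume that all 15 places per group are filled and both visits are completed. Units are SDs of the change score. With equal variances at T0 and T1 and correlation ρ, the ANCOVA residual SD is √((1 + ρ)/2) times the change-score SD. ANCOVA is therefore at least as precise, apart from one degree of freedom.

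**The case against.** The strongest reply is that the only formal physiology hypothesis, H2.4, is already a randomized between-arm comparison of change. Shared drift cancels there, and Group 3 is the right comparator for its question, an additive effect of the oil. This stands. A reader might infer that H2.4 is biased, or that habituation counts as treatment effect throughout the physiology analysis. The article does not support that.

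The reply continues that Group 4 is not excluded. Section 2.8 speaks of change across groups, the sentence before it expects the before-after effect to differ by intervention, and a full analysis plan that is not shown may name Group 4. This stands in part: it would be too strong to say that Group 4 is left out of the physiology analysis. But the sentence on attribution rests on two time points, not on arms, and H2.4 fixes Group 3 alone, whereas H1 and H2.2 name Group 4 explicitly. The point is about a stated inference, not a missing model.

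Third, no within-arm test is specified anywhere. This is correct. The 11-44% and 19-75% figures show how a before-after reading would behave under an assumed drift; they are not error rates of a planned analysis.

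Fourth, regression to the mean is a poor example of shared change here, because participants are selected on GAD-7 and PHQ-9, not on HRV or PWV. This also stands, and the point does not rely on it; second-visit familiarity is enough.

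Finally, the substudy is exploratory. That limits what is at stake to interpretation, but it does not make a before-after change causal.

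**Conclusion.** The point holds in a limited form. Section 2.8 draws a causal conclusion about each intervention that a T0-T1 comparison cannot support. The one named contrast is sound but covers only the oil increment. No named physiology contrast estimates the effect of hypnosis alone, or of hypnosis plus oil, against the control arm, although up to 15 controls are recorded and Section 2.6 gives that arm exactly this role.

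The size depends on the shared change, which is unknown. If it is nil, before-after change misleads no one. At an assumed 0.5 SD, a single arm would appear to respond in about 44% of cases with no treatment effect, and Groups 1 and 2 pooled in about 75%. The consequence is confined to interpreting an exploratory substudy; the primary analysis is unaffected.

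**What to change.** In Section 2.8 and H2.4:

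- Base attribution on baseline-adjusted between-arm differences at T1 (ANCOVA on the T1 index with the T0 index as covariate), and reword the sentence on change caused by the interventions to match.
- Keep Groups 1/2 versus Group 3 for the oil increment.
- Name Group 4 as the reference for hypnosis only and for hypnosis plus oil.
- Report within-arm T0-T1 change descriptively.
- Present all contrasts as exploratory estimates with confidence intervals, not as powered tests.

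The cost is some rewording and two further exploratory contrasts on recordings already planned. The downside is wide intervals with only 15 controls, and within-arm changes that will look less impressive once set against Group 4.
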